## Abstract

**Background:**

Mosquito-borne viruses are imposing an ever increasing health burden worldwide. In addition to the recent Zika and chikungunya virus epidemics, dengue viruses have become the fastest growing problem with a 40-fold increase in the number of reported cases over the past five decades. Current mosquito control techniques involving larval source reduction, larviciding, and space spray of adulticides are costly, laborious, and of debatable efficacy. There remains an urgent need for the development of intervention methods that can be reasonably implemented in the context of modern day urbanisation. Auto-dissemination (AD) of insecticide by adult mosquitoes offers a potentially practical and useful tool in an integrated vector control programme. Recently, an immediately employable AD device, the In2Care® mosquito trap, has been commercialised and shows promise as an effective tool. However, there remains a lack of demonstration of epidemiological efficacy.

**Methods/design:**

This trial aims to assess the extent to which implementation of In2Care® mosquito traps can reduce vector *Aedes* (*Stegomyia*) spp. adult mosquito densities and dengue virus transmission as measured by sequential sero-conversion rates in children 6–16 years of age in a dengue endemic location: Lipa City, Philippines. To achieve this, we will carry out a parallel, two-armed cluster randomised trial evaluating AD efficacy for reducing the incidence of dengue over a 2-year period with 4 consecutive months of vector control during peak dengue transmission each year.

**Discussion:**

For decades, it has been commonly accepted that an integrated approach to mosquito control is required. The World Health Organization (WHO) Global Strategic Framework for Integrated Vector Management recommends a range of interventions, in combination, to increase control impact to reduce transmission. This efficacy trial of the first commercial product using the AD approach will be informative in assessing the general utility of AD in reducing not only adult vector densities but, more importantly, reducing the incidence of dengue. The AD technique may complement source reduction and larviciding campaigns by more efficiently targeting the most productive containers and those beyond human reach. If successful, this mosquito control strategy could prove an invaluable tool in the fight against urban mosquito vectors and a reduction in the burden of associated disease.

**Trial registration:**

ISRCTN44272773. Registered on 31 January 2019.

**Electronic supplementary material:**

The online version of this article (10.1186/s13063-019-3376-6) contains supplementary material, which is available to authorized users.

## Background

Mosquito-borne viruses of public health importance are imposing an ever increasing burden worldwide. In addition to the recent notable epidemics of West Nile, Zika, and chikungunya viruses, the dengue viruses in particular have become the fastest growing problem with a 40-fold increase globally in the number of reported cases over the past five decades affecting over 100 countries [1]. Currently, an estimated 400 million dengue virus (DENV) infections occur annually, of which only a quarter or less become symptomatic [2]. Of these, a small percentage manifest into more severe forms of the disease: dengue haemorrhagic fever and/or dengue shock syndrome and potentially death. The primary mosquito species responsible for DENV transmission is *Aedes aegypti* (L.), a species that has adapted to an urban habitat, proliferating in artificial water containers arising primarily from solid waste and frequent long-term water storage. Rates of urbanisation are increasing dramatically globally, particularly in regions of high socio-economic vulnerability, exacerbating an already over-stretched infrastructure and low public service capacity. The increasing frequency and amplitude of dengue epidemics bears testament to the scale of the threat and the urgent need to address these diseases in the context of a rapidly changing urban landscape [3].

Despite progress in the development of vaccines for preventing chikungunya, dengue, and Zika infections [4–6], no current candidates appear likely to have general application in endemic areas. Therefore, it is generally agreed that an integrated approach to control, including a significant role for vector abatement, will be required [7, 8]. For over 100 years, the most common dengue control strategy has been source (larval habitat) reduction and focal insecticide treatment of mosquito larval habitats (so-called ‘breeding sites’). This approach helped to eliminate *Ae. aegypti* from 22 countries in the Americas during control campaigns in the 1950s and 1960s [9]. However, these activities required enormous human resources and costs to support, making them unsustainable in the long term. Today, the scale of continuing urban expansion abnegates such an approach. Current mosquito control techniques based on larval habitat source reduction, larviciding, and space spray are costly, laborious, and of debatable efficacy depending on the circumstances [10, 11]; therefore, there remains an urgent need for the development of intervention methods that could be reasonably implemented in the context of modern day urban environments and with some measure of possible sustainability. One of the major challenges in large, condensed urban settings is achieving sufficient coverage of aquatic habitats preferred by *Ae. aegypti* [12]. Identifying and treating all possible breeding sites manually is not a realistic solution even with considerable organised community support and resources.

One potential solution, originally proposed by Itoh et al. [13], is to exploit the ‘skip-oviposition’ behaviour of adult female *Ae. aegypti* to disseminate insecticide to natural larval habitats [14], in other words female mosquitoes exposed to a surface contaminated with insecticide subsequently spread it to other aquatic sites during oviposition [12, 15], a mechanism called auto-dissemination (AD). Insofar as the mosquitoes cannot “carry” substantial amounts of the particulate chemical matter on their tarsi and the insecticide must work in even large volumes of water, the insecticide must be potent at very minute (nanogram) concentrations. Furthermore, given the relatively indiscriminate dissemination of the insecticide, it must also be non-toxic to vertebrates and have a relatively narrow range of action against other aquatic invertebrates. Pyriproxyfen (PPF) ticks all the boxes [16]. This World Health Organization (WHO) approved pupacide can be safely used in drinking water and is recommended as part of conventional programmes against *Ae. aegypti* [17, 18]. It is a synthetic analogue of juvenile hormone which, at very low concentrations, prevents larval and pupal development as well as female fertility and male spermiogenesis [19, 20]. Currently it is applied as either granular or liquid formulations directly to water containers and drains in South America and South East Asia with documented success in reducing immature and adult mosquito numbers and has been associated with a reduction in dengue incidence [21, 22]. The potential of PPF application via AD has been demonstrated in a variety of small-scale trials in Peru and Italy [12, 15] and on a larger scale in the Amazon [23]. However, whilst entomological efficacy of PPF has been demonstrated when applied through AD, ground space spray, or container treatment, evidence of actual epidemiological impact (infection reduction) is generally inconclusive [24, 25].

Recently, a commercialised AD device, the In2Care® mosquito trap (In2Care® BV, Wageningen, Netherlands) [26], has been validated in field studies in the Grand Cayman, yielding pupal mortality rates of ~ 60% (unpublished data). The In2Care® trap attracts ovipositing *Ae. aegypti* females, which are then contaminated with a combination of PPF and an entomopathogenic fungus, *Beauvaria bassiana*, a United States Environmental Protection Agency approved agent that has been used in biological control of many agricultural pests for decades [27]. The lethal and pre-lethal (e.g. reduced feeding propensity) effects of the fungus have been described in *Anopheles* and *Aedes* species in which it takes several days to kill the adult insect, thereby allowing the mosquito to disseminate the PPF component [28, 29]. The fungal infection also interferes with DENV replication within the mosquito, thus having a profound effect on mosquito vectorial capacity (i.e. transmission efficacy) beyond that of shortening the adult mosquito lifespan [30]. The In2Care® mosquito trap thus uses an AD approach to disseminate a pupacide combined with a direct action, slow-acting entomopathogenic adulticide.

This study proposes to evaluate the epidemiological and entomological efficacy of the In2Care® trap in a dengue-endemic urban location in the Philippines.

## Methods/design

### Objectives

The primary objective of the trial is to assess the extent to which implementation of In2Care® mosquito traps can reduce *Ae. aegypti* adult mosquito densities and DENV sero-conversion rates (i.e. transmission) in children 6–16 years of age in a site of endemic dengue risk in the Philippines.

### Study type

The study is a parallel, two-armed cluster randomised trial (PCRT) evaluating the efficacy of the In2Care® mosquito trap for reducing incidence of dengue infection over a 2-year period using 4 consecutive months of treatment each year.

Previous studies have estimated that, to account for the unpredictable spatio-temporal heterogeneity in dengue transmission, PCRTs are the most effective study design and that a larger number of clusters with fewer children per cluster provide the optimal strategy—in effect, a bet-hedging approach for a statistically sufficient coverage of an area [31]. In order to attempt to control for the spatial heterogeneity in dengue occurrence, 46 areas (hereafter referred to as “clusters”), each of approximately 200 m in radius, will be pre-selected. Twenty-three clusters will be assigned to the treatment arm with In2Care® traps and 23 to the control arm without traps. Cluster sites assigned to treatment versus control arms will be matched according to retrospective incidence of reported dengue clinical cases over the previous 5 years and human population density (See Stratification scheme below). Because of ‘edge effects’, where individuals near the periphery of the treatment area will be potentially subject to contact with mosquitoes coming from neighbouring non-treated areas, we will implement the “fried egg” design [32] whereby we will assess sero-conversion only in children resident at least 50 m from the treatment zone edge. Thus, whilst we will implement In2Care® traps throughout a 200 m radius circle, we will only consider sero-conversion in children within a 150 m radius (Fig. 1). One hundred schoolchildren (between 6 and 16 years of age) will be recruited for repeated sero-conversion observation within the inner circle of each of the 46 clusters (See Sample size calculations below). As the population density in clusters will vary, it is possible that there will not be sufficient children within a prescribed area. In this case, we will increase the circle radius to reach the required sample number.

**Fig. 1 Fig1:**
[figure not shown]
Intervention and sampling strategy. The yellow region includes recruited children for the sero-conversion study and the outer peripheral region is the buffer zone also treated with AD devices (blue jar icons) but without sero-conversion saliva sampling

Adult *Aedes* mosquito densities will be monitored in treatment and control sites by the use of Gravid *Aedes* Traps (GATs; Biogents AG, Regensburg, Germany) (Additional file 1). GATs are more efficient in capturing gravid *Ae. aegypti* than sticky ovitraps and are practical, low cost, and easily transportable devices, essential attributes in large-scale monitoring programmes [33].

### Stratification scheme

Clusters will be stratified according to historical dengue incidence and population density. In the Philippines, a *barangay* is the smallest administrative division in the Philippines (urban or rural), but which can be subdivided into *puroks* (zones) consisting of 20 to 50 households depending on the location and density of the households in an area. The previous 5 years of dengue incidence data at the *purok* administrative unit level will be acquired from the Philippines Integrated Disease Surveillance and Response (PIDSR) system to identify relative defined ‘hotspots’ and ‘coldspots’ of dengue activity during that period. This information will be entered into the Disease Data Management System (DDMS+) (see Data management below) along with information on geography, population density, and infrastructure at the *barangay* level. This will generate maps with which to choose clusters for the intervention study and assign clusters to either treatment or control groups according to broad similarities.

### Sample size calculations

The sample size is calculated using the following standard formula when considering proportions (incidence rate):$$ n=2{\left(\mathrm{Za}+\mathrm{Z}1-\upbeta \right)}^2\ \mathrm{p}\left(1-\mathrm{p}\right)/{\left(\mathrm{p}0-\mathrm{p}1\right)}^2 $$

Where *n* is the required sample size per treatment arm (control or treatment), Zα and Z1–β are constants set by convention according to the accepted α error and whether a one-sided or two-sided effect, p0 is the proportion infected in control areas, and p1 the proportion infected in treatment areas (p = (p0+p1)/2).

Assuming a *p* < 0.05 as acceptable and a study with 90% power, the following constant values are: Zα = 1.96 (two-tailed); Z1–β = 1.2816.

The final sample size will depend on the dengue transmission rate in the study areas as estimated from the historical mean rate. Recent sero-conversion studies in Cebu City, Philippines, have observed a symptomatic incidence rate of 1.6 per 100 person-years (1.6%) with 7% subclinical infections in the general population, increasing to 7% symptomatic cases and 17% subclinical infections in children < 15 years old [34]. Historical annual incidence rates were estimated at between 11 and 22% [35]. Reported incidence rates in our study area (under administrative Region IV-A) are consistently amongst the highest in the country. To be conservative, however, we estimate an infection incidence of 3% (to include symptomatic and subclinical infections). For an efficacy of treatment of 50% (i.e. reduction in dengue), with 90% power, a minimum of 2054 children (aged 6–16 years old) will need to be recruited in treatment sites with an equivalent number in matched control sites and followed for 2 years. We factor in a drop-out of 250 children (~ 12.2%) per treatment and control arm (500 total) over the 2-year period. Thus, the total number of children to be recruited is 4600, distributed over 46 clusters of 100 children each.

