## Study limitations

The major concern of the study will be the dependency on there being sufficient dengue activity during at least one of the study years and that the cluster design is sufficient to account for the recognised spatio-temporal heterogeneity in dengue [58, 59]. To maximise power and somewhat alleviate this concern, sero-conversion rather than dengue case incidence will be used as the measure of epidemiological outcome, capturing the sub-clinical infections that form the majority of dengue infections [60, 61]. Continued compliance of participants during the 2 years may pose a problem as will community acceptance of the In2Care® traps and GAT devices. Considerable effort will be given to continuous dialogue with the community to maintain adherence throughout the study.

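### The stated 90% power comes from a formula for independent children; with 23 clusters per arm it holds only if there is no between-cluster variation.

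*Protocol article*

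**What the plan says.** The Sample size calculations section prints the two-proportion formula with its inputs: control infection 3%, efficacy 50% (so 1.5% under treatment), two-sided 5% significance (1.96) and 90% power (1.2816). It concludes that "with 90% power, a minimum of 2054 children" are needed in the treatment sites and as many in the control sites. It then adds 250 per arm for drop-out and divides the result into clusters: "Thus, the total number of children to be recruited is 4600, distributed over 46 clusters of 100 children each".

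Elsewhere the article treats the cluster as the unit that matters. The Study type section assigns 23 clusters to each arm and explains the choice of a parallel cluster design as a way "to account for the unpredictable spatio-temporal heterogeneity in dengue transmission". The Statistical analyses section (Sero-conversion) fits cluster ID as a random factor. The Study limitations section lists among the main concerns whether "the cluster design is sufficient to account for the recognised spatio-temporal heterogeneity in dengue".

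**The concern.** Children in one cluster live within roughly 150 m of each other, share the same mosquito population and receive the same allocation. Their outcomes are correlated, so 2054 children in 23 clusters carry less information than 2054 independent children. The planned analysis allows for that correlation through the cluster random effect, while the sample size sets it to zero. The analysis will therefore produce wider intervals than the power statement implies.

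This is the article's only power statement for its principal outcome. If it is too high, a null result will be read as fair evidence against the traps when the trial may have had a much smaller chance of detecting the effect it was planned for.

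**Working it through.** **Inputs.** From the Sample size calculations section: p0 = 0.03, p1 = 0.015, mean p = 0.0225, z-values 1.96 and 1.2816, 2054 per arm, 250 per arm for drop-out. From the Study type section: c = 23 clusters per arm. Analysed cluster size: m = 2054/23 = 89.3. The ICC and k values below are assumptions, because the document gives none.

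**Step 1: reproduce the stated figure.** n = 2 × (1.96 + 1.2816)² × p(1 − p)/(p0 − p1)² = 2 × 10.508 × 0.021994/0.000225 = 2054.3. This is the stated 2054. Adding 250 gives 2304, rounded to 2300 per arm = 23 × 100. Drop-out is the only inflation, so the figure contains no allowance for clustering.

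**Step 2: power on the ICC scale.** Design effect DE = 1 + (m − 1) × ICC. Power = Φ(√[(2054/DE) × 0.015²/(2 × 0.0225 × 0.9775)] − 1.96). Example at ICC 0.01: DE = 1 + 88.3 × 0.01 = 1.88; effective n = 2054/1.88 = 1091; √(1091 × 0.000225/0.0439875) = 2.36; Φ(2.36 − 1.96) = 66%.

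| ICC | DE | Power, 2054 per arm | Power if all 2300 are kept (m = 100) | Efficacy detectable with 90% power (2054 per arm) | Clusters per arm for 90% power (m = 89.3) |
|---|---|---|---|---|---|
| 0 | 1.00 | 90% | 93% | 50% | 23 |
| 0.005 | 1.44 | 77% | 80% | 58% | 34 |
| 0.01 | 1.88 | 66% | 68% | 65% | 44 |
| 0.02 | 2.77 | 50% | 51% | 76% | 64 |

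If no child dropped out, power would still fall below 90% at an ICC of about 0.0013 and would be down to about 80% at 0.005. The drop-out margin does not rescue the claim.

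**Step 3: power on the k scale (Hayes–Bennett, unmatched).** v = p0(1 − p0)/m + p1(1 − p1)/m + k²(p0² + p1²). Power = Φ(√[(c − 1)(p0 − p1)²/v] − 1.96). Example at k = 0.5: v = 0.000326 + 0.000165 + 0.000281 = 0.000773; √(22 × 0.000225/0.000773) = 2.53; Φ(2.53 − 1.96) = 72%.

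| k | Power with c − 1 | Power without the one-cluster correction |
|---|---|---|
| 0 | 89% | 90% |
| 0.25 | 84% | 86% |
| 0.5 | 72% | 74% |
| 0.75 | 56% | 57% |

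**Step 4: relate the two scales.** ICC is approximately k²p/(1 − p). At p = 0.0225 to 0.03, k = 0.25, 0.5 and 0.75 correspond to ICCs of about 0.0014–0.0019, 0.006–0.008 and 0.013–0.017. An ICC of 0.02 implies k of about 0.8–0.9, just beyond the k range shown. An ICC of 0.05 (DE 5.42, power 29%) implies k of about 1.3–1.5; it is an extreme case, and the conclusion does not rely on it.

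**The case against.** The strongest reply is that 3% was chosen to be conservative. The same section cites 7% symptomatic plus 17% subclinical infection in children under 15 in Cebu City, and historical annual rates of 11–22%. With 2054 per arm and 50% efficacy, power at ICC 0.01 would be 92% at 6% control risk and 99.7% at 11%; at ICC 0.02 it would be 80% and 97%. On the k scale the relief is smaller: at k = 0.5, 87% and 94%; at k = 0.75, only about 66% and 72%. A higher true risk could thus absorb some clustering. But the article does not offer the 3% as a substitute for a design effect. It ties both 90% power and 2054 to 3%, and its limitations section worries about too little dengue activity.

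Second, clusters are matched or stratified on five-year incidence and population density, and the model adjusts for baseline site risk. The relevant variance is what remains after that, so the unmatched k values above should be read as residual k. This is fair, but the article quantifies no reduction, and residual variation would have to be zero for the stated power to hold.

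Third, many clusters with fewer children is an efficient design, and the article names heterogeneity as a concern. Both are true. Yet at 89 children per cluster even an ICC of 0.005 gives a design effect of 1.44, and naming the concern does not correct the figure.

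Finally, the arithmetic itself is right. The fault is in the choice of formula, which omits clustering. Condensation into an article does not explain it, because the printed formula yields the printed number.

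**Conclusion.** The concern holds. At the stated 3% versus 1.5%, 23 clusters per arm with 2054 analysed children give 90% power only if between-cluster variation is zero; any positive ICC takes it lower. Over ICC 0.005 to 0.02 power is 77% to 50%, and over k 0.25 to 0.75 it is 84% to 56%.

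These are sensitivity figures, not estimates. They rest on assumed ICC or k values, a control risk of 3%, equal cluster sizes and no gain from matching or covariate adjustment. A higher infection risk or effective matching would reduce the loss, but neither is claimed or quantified as an allowance for clustering. The power statement needs correcting before it is used to interpret the result.

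**What to change.** In the Sample size calculations section:

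- Replace the individual-level formula with a cluster version: either n × [1 + (m − 1) × ICC], or the Hayes–Bennett formula with k, in matched form if matching is kept in the analysis.
- State the assumed ICC or k and its basis. The five-year purok-level incidence data that the trial already acquires are a starting point for k, after removing small-count sampling noise. They are reported clinical cases in units of 20 to 50 households, whereas the outcome is sero-conversion in larger circles, so present a range around the estimate.
- Report the power of 23 clusters per arm for 50% efficacy, and the minimum detectable efficacy, over that range. If the higher infection rates cited are meant to absorb clustering, say so and show the figures.
- Remove the unqualified 90% power.

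The section already says that the final sample size depends on local transmission, so revisiting it fits the plan. The cost is rewording one section and a less favourable stated power. No extra enrolment is asked for.

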### Setting (Fig. 2)

Dengue is endemic throughout much of the Philippines, and between 2008 and 2012 the country’s Department of Health (DoH) reported an annual average of 117,065 diagnosed (symptomatic) dengue cases, although the number is likely to be far higher because of significant under-reporting [36]. Region IV-A (Calabarzon) has consistently had a high burden of dengue and was one of three regions where the dengue vaccine (Dengvaxia®, Sanofi Pasteur) was implemented. According to an official DoH report, in 2018 the Calabarzon region was the area most affected by dengue, accounting for 19% of all national cases, while also showing an increase in case load of 40% in comparison with the same time period the previous year. Lipa City is a large city in the Calabarzon region and is located approximately 78 km south of Manila at an altitude of 312 m, covering an area of 209.40 km^2^ with a population of 332,386 people in 2015. The city is subdivided into 72 *barangay*s of varying human density (at an average of ~ 1800/km^2^). The average annual temperature is 28 °C (82 °F) and the peak dengue transmission season typically occurs during increased rains from June to December.

